#### Cost-effectiveness

Both participant and researcher time costs will be multiplied by standard staff costs (including on-costs) to estimate the financial cost of using each method on a per-person basis. Differences in time cost and total financial cost will be compared across methods using a repeated measures analysis of variance test. P<.05 will be considered statistically significant. If statistically significant differences exist, differences in cost-effectiveness will be assessed using the same procedure. Cost-effectiveness will be defined as the cost per person to reduce the absolute misestimation of energy intake by 1% point.

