**Methods:**

Using a controlled feeding study design, 24HR data collected using 3 methods will be obtained for comparison with observed intake. A total of 150 healthy adults, aged 18 to 70 years, will be recruited and will complete web-based demographic and psychosocial questionnaires and cognitive tests. Participants will attend a university study center on 3 separate days to consume breakfast, lunch, and dinner, with unobtrusive documentation of the foods and beverages consumed and their amounts. Following each feeding day, participants will complete a 24HR process using 1 of 3 methods: the Automated Self-Administered Dietary Assessment Tool, Intake24, or the Image-Assisted mobile Food Record 24-Hour Recall. The sequence of the 3 methods will be randomized, with each participant exposed to each method approximately 1 week apart. Acceptability and the preferred 24HR method will be assessed using a questionnaire. Estimates of energy, nutrient, and food group intake and portion sizes from each 24HR method will be compared with the observed intake for each day. Linear mixed models will be used, with 24HR method and method order as fixed effects, to assess differences in the 24HR methods. Reporting bias will be assessed by examining the ratios of reported 24HR intake to observed intake. Food and beverage omission and intrusion rates will be calculated, and differences by 24HR method will be assessed using chi-square tests. Psychosocial, demographic, and cognitive factors associated with energy misestimation will be evaluated using chi-square tests and multivariable logistic regression. The financial costs, time costs, and cost-effectiveness of each 24HR method will be assessed and compared using repeated measures analysis of variance tests.

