## Methods

### Sample and Recruitment

The sample will be selected from adults aged 18-70 years residing in Perth, the capital city of Western Australia, Australia, and recruited via the electoral roll by selecting postcodes that provide representation across socioeconomic status. Other recruitment methods will include advertising on the Curtin University website and a snowball methodology (eg, email newsletter and referrals from friends or colleagues). A final sample of 150 randomized participants (allowing for a 20% dropout) will allow for 90% power at a 5% significance level when the true difference between any 2 mean differences between estimated and observed dietary energy intake is 0. Quota sampling will be used to ensure that equal numbers of men and women are recruited. To be included in the study, participants must be able to attend in-person feeding sessions on 3 separate days and have access to a computer and a smartphone (running iPhone operating system or Android operating system) with a data plan. Exclusion criteria include serious illnesses or medical conditions, pregnancy, special dietary requirements, or dietary restrictions because of food allergies or intolerances or dieting to lose weight.

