### Data Analyses

#### Energy Intake Estimation Accuracy

The participant feeding days with at least two meals eaten at the food laboratory will be included in the analyses. Daily energy intake from each 24HR method and the controlled feeding sessions will be calculated, excluding any items reportedly consumed outside of the food laboratory. Outlier checks will be conducted to identify any obvious keying errors or food composition data anomalies, which will be corrected before proceeding. Bland-Altman plots will be used to test for agreement between the 24HR values and controlled feeding measures at the individual and group levels. Repeated measurements will be analyzed using the linear mixed models procedure using SPSS version 25, accounting for age, gender, and BMI, with 24HR method and method order as fixed effects, to assess whether there are statistically significant differences by 24HR method. Misreporting will be assessed by examining the ratio of reported 24HR intake to observed intake, with the lowest tertile considered to indicate underreporting. The proportion of underreporters in each 24HR method will be compared using chi-square tests and logistic regression. Among underreporters, the total energy misestimation will also be compared using regression models adjusted for age, gender, and BMI.

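### Time and cost are compared by repeated measures ANOVA, which in its standard form drops incomplete participants and has no visit term; a mixed model would recover precision at almost no cost

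*Protocol article*

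**What the plan says.** - **Cost analysis.** The Cost-effectiveness section states: "Differences in time cost and total financial cost will be compared across methods using a repeated measures analysis of variance test". The abstract says the same of financial costs, time costs and cost-effectiveness, which "will be assessed and compared using repeated measures analysis of variance tests". Neither place names a visit, period or order term.
- **Gate.** The same section adds: "If statistically significant differences exist, differences in cost-effectiveness will be assessed using the same procedure".
- **Accuracy analysis.** Under Energy Intake Estimation Accuracy: "Repeated measurements will be analyzed using the linear mixed models procedure using SPSS version 25", "with 24HR method and method order as fixed effects, to assess whether there are statistically significant differences by 24HR method". Data enter by feeding day, provided at least two meals were eaten in the laboratory, so a participant may contribute fewer than three days.
- **Dropout.** Under Sample and Recruitment: "A final sample of 150 randomized participants (allowing for a 20% dropout) will allow for 90% power at a 5% significance level".
- **Design.** Three periods on separate days about a week apart, with the order of methods randomised for each participant.

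**The concern.** The trial has three visits and expects some participants not to complete all of them. A standard repeated measures ANOVA needs all three values from each person, so one missing method also removes that person's other recalls. A mixed model keeps them. The ANOVA as described also leaves any change in time across visits in the error term. The energy model carries an order term, and the model for method preference adjusts for order, so the cost analysis is the exception within the plan.

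A further point is that mFR24 time includes training, an interview and researcher coding, while the other two tools are self-administered. Equal variances of the pairwise differences, which the uncorrected ANOVA assumes, are therefore doubtful.

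At stake is the precision of the time and cost contrasts and, through the gate, whether cost-effectiveness is compared. Cost-effectiveness is in the study title and the first objective.

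**Working it through.** **Inputs from the protocol.** 150 randomised, 20% dropout, three methods per person, random order.

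**Inputs assumed, because the protocol gives none.** ICC 0.3 to 0.7; total SD set to 1; 30 incomplete participants; linear change per visit *d* of 0 to 0.5 SD.

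**1. The plan's own figure.** 120 / (1 − 0.20) = 150, so 150 randomised means 150 × 0.80 = 120 completers. The 90% power cannot be reproduced, since no margin or SD is given. It concerns energy intake rather than cost, and nothing below depends on it.

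**2. Recalls set aside by complete-case ANOVA.** Completers give 120 × 3 = 360 recalls.
- 15 leave after visit 1 and 15 after visit 2: 360 + 15 + 30 = 405 collected, 45 set aside (11.1%).
- All 30 leave after visit 2: 360 + 60 = 420 collected, 60 set aside (14.3%).

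These are counts of recalls, not of information, so the next step is needed.

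**3. Information lost by exclusion, by hand.** With 120 completers the variance of a contrast is 2(1 − ICC)/120. Suppose 30 people have two visits, spread evenly over the three pairs of methods. Each method then appears 60/3 = 20 times, and the efficiency of blocks of two for three treatments is 3/4, so they are worth 20 × 3/4 = 15 completers. The variance ratio of ANOVA to mixed model is (120 + 15)/120 = 1.125. People with one visit or none add no within-person information (ratio 1.00). Recovery of between-person information adds a little at low ICC.

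**4. The same by simulation.** 150 participants, simple randomisation to six sequences, 300 runs per scenario, mixed model with method and period, no visit effect:

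| The 30 incomplete participants have | Variance ratio, ANOVA / mixed model |
|---|---|
| no visits | about 1.00 |
| the first visit only | about 1.0 to 1.06 |
| the first two visits | 1.07 to 1.17 |

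With 300 runs these carry Monte Carlo error; they are consistent with step 3. At the upper end, √1.17 = 1.08, so intervals are about 8% wider.

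**5. Visit effect left in the residual.** The inflation factor is 1 + *d*²/(1 − ICC):

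| Change per visit | ICC 0.3 | ICC 0.5 | ICC 0.7 |
|---|---|---|---|
| 0.1 SD | 1.01 | 1.02 | 1.03 |
| 0.25 SD | 1.09 | 1.13 | 1.21 |
| 0.5 SD | 1.36 | 1.50 | 1.83 |

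The example at 0.5 SD and ICC 0.5 is 1 + 0.25/0.5 = 1.50.

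**6. Both together.** At 0.5 SD per visit the simulated ratio ran from 1.33 to 2.23 across dropout patterns, so intervals are 15% to 49% wider (√1.33 = 1.15, √2.23 = 1.49).

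**7. Bias.** The mean error of the contrast was about 0 in every scenario for both analyses. Dropout related to time or cost was not simulated.

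**The case against.** The strongest reply is that this is a modest efficiency point. Order is randomised, so visit effects do not systematically favour a method. Each tool is used once, so a practice effect across different tools is an assumption, and at 0.1 SD per visit it costs 1 to 3% in residual variance. The sample size was set for energy, not cost. Complete-case deletion and uncorrected sphericity are defaults of the named test, not statements in the article, and their handling may sit in an analysis plan that is not shown. All of this stands and limits the size of the point. It does not remove it, because the article fixes the test in two places when a better-suited procedure is already planned.

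Three stronger readings are tempting, and the documents do not support them:
- **Cost from completers, accuracy from all eligible days.** A reader might infer that people who stop vanish from the cost side alone. The plan assesses cost-effectiveness by the same procedure as cost, so exclusion could apply to both sides. It does not say that the accuracy input is taken from the energy mixed model.
- **Cost biased towards easier users.** This requires dropout related to time or difficulty. It is possible, but nothing in the documents shows it. Because comparisons are within person, generally faster completers do not by themselves bias the contrasts.
- **The planned mixed model, copied as it stands, cures the visit problem.** Its method order term may mean sequence rather than visit, and a sequence term does not adjust for visit.

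**Conclusion.** The concern holds as a loss of precision. Excluding incomplete participants raises contrast variance by about 0 to 17%, depending on when the 30 assumed dropouts leave and on an ICC between 0.3 and 0.7. Leaving out visit adds from almost nothing to a substantial amount; with exclusion included, the ratio is about 1.3 to 2.2 at 0.5 SD per visit. The ICC, dropout timing and visit effect are assumptions. The visit part of the simulated spread also assumes simple randomisation. With exactly balanced sequences the contrast itself would be protected, but the ANOVA's residual would still be inflated by the factor in step 5 and the test would be conservative.

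The 11% and 14% of recalls set aside should not be read as the share of information lost. Systematic bias is not established. The gate passes the loss of precision on to the cost-effectiveness comparison. The change is worth making because it is specific and nearly free, not because the planned analysis would be invalid.

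**What to change.** In the Cost-effectiveness section and the abstract, replace the repeated measures ANOVA for time cost and total financial cost with a linear mixed model:
- method and visit as fixed effects, with visit named explicitly as period, not as method order;
- participant as random effect;
- all completed eligible feeding days included, whether or not the participant finished all three;
- residual variances allowed to differ by method;
- the original scale, so that results stay arithmetic mean costs per person, with bootstrap intervals if costs are skewed.

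A log transformation is not a substitute, because it compares geometric means while the plan needs cost per person. Participants who leave before any visit cannot be recovered by either analysis.

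The cost is a change of wording. The data are the same and the linear mixed models procedure is already planned in the same software; only the bootstrap, if needed, adds a little programming.

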### Cost and Cost-effectiveness of Measures

Both financial and time costs for participants to use each of the methods will be assessed. The time spent by researchers and participants in the administration of each 24HR method will be recorded for each participant. This includes time spent training individuals to take the mFR24 images, time spent completing the 24HR interview, and any time spent supporting individuals to complete their 24HR interviews. The time spent by researchers coding the mFR24 data will also be recorded. Both ASA24 and Intake24 have the capability to collect time stamp data to identify how much time the participants spend inputting data. All other time data, including time spent cleaning the data, will be manually collected by researchers.

Financial costs, such as server space for digital data storage, will be recorded. After converting the time data to a financial cost, the total cost data will be considered in parallel with the measures of accuracy derived for the 3 methods. The primary accuracy measure for cost-effectiveness is the absolute percentage error in energy intake. Comparing costs with accuracy will identify whether any of the 3 methods are dominated by another (ie, is more expensive and less accurate). If not, the cost per person to reduce absolute misreporting by 1% point will be estimated.

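### The planned repeated measures ANOVA of cost-effectiveness, and its gate on cost significance, do not fit the protocol's own definition of cost-effectiveness, which is a ratio between two methods

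*Protocol article*

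**What the plan says.** Three places in the protocol article bear on this.

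- **Data Analyses, Cost-effectiveness.** Costs come first: "Differences in time cost and total financial cost will be compared across methods using a repeated measures analysis of variance test", with "P<.05 will be considered statistically significant". Then: "If statistically significant differences exist, differences in cost-effectiveness will be assessed using the same procedure". The quantity is fixed in the same paragraph: "Cost-effectiveness will be defined as the cost per person to reduce the absolute misestimation of energy intake by 1% point".
- **Abstract, Methods.** The same test is named, without a gate: "The financial costs, time costs, and cost-effectiveness of each 24HR method will be assessed and compared using repeated measures analysis of variance tests".
- **Cost and Cost-effectiveness of Measures.** The effect measure is set: "The primary accuracy measure for cost-effectiveness is the absolute percentage error in energy intake". Cost and accuracy are then looked at together: "Comparing costs with accuracy will identify whether any of the 3 methods are dominated by another (ie, is more expensive and less accurate"). The ratio follows where no method is dominated: "If not, the cost per person to reduce absolute misreporting by 1% point will be estimated". No P value on cost is required.

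None of these places names a comparator method or says how a value per participant and method would be formed.

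**The concern.** The definition, the test and the trigger are all fixed in one paragraph, and they do not fit together. A repeated measures ANOVA across three methods needs one outcome value per person for each method. The defined quantity exists only for a pair of methods. The trigger also differs between the two cost sections: one asks for a significant cost difference, the other for absence of dominance.

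Cost-effectiveness is in the title and in the first objective, and the Strengths and Limitations section offers it to policy makers and survey planners. If the test were run on per-person ratios, the P value would describe a quantity that is not the one defined, and the average behind it could easily have the wrong sign. If the gate were followed literally, the formal comparison would be skipped when costs are similar, although a difference in accuracy would then decide the matter.

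**Working it through.** The protocol gives no figure for this analysis, so there is none to reproduce. The check has a structural part, which needs no assumptions, and an illustration, which does.

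**1. Is there a per-person value for each method?** For methods A and B the defined quantity is (cost of A − cost of B) / (absolute error of B − absolute error of A). Three methods give three pairwise ratios, or two against a reference, and none for a method on its own. Two ways of forcing a per-person value:

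- *Cost divided by error within each method.* This is computable but is not the defined quantity, and it can misrank. At an equal cost of 25, a method with 10% error scores 25/10 = 2.5 per point and one with 30% error scores 25/30 = 0.83, so the less accurate method looks better.
- *Pairwise ratio per person.* The denominator is a difference of two absolute errors, which passes through zero and changes sign, so the ratio has no stable mean. A negative value can mean either cheaper and better or dearer and worse. The mean of such ratios is also not the ratio of the mean differences.

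**2. Illustration.** From the protocol: 150 × (1 − 0.20) = 120 completers. Assumed, because the documents give no cost or error SDs: normal percentage errors with the means and SDs below, within-person correlation 0.3, and a cost difference with SD 10. There were 4,000 runs per scenario.

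The target ratio uses E|X| = s√(2/π)·exp(−m²/2s²) + |m|(1 − 2Φ(−|m|/s)). For scenario b, E|A| = 15 × 0.798 = 11.97 and E|B| = 15.96 × 0.8825 + 10 × 0.383 = 17.91. The gap is 5.94 and the target is 30/5.94 = 5.05.

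| Scenario: error mean (SD), A; B; cost difference | Ratio of means: median (95% range) | Mean of per-person ratios: median (95% range) | Mean ratio negative | Denominator ≤ 0 |
|---|---|---|---|---|
| a: 0 (20); −10 (20); 30 | 12.5 (−141 to 149) | 0.12 (−37 to 33) | 49% | 46% |
| b: 0 (15); −10 (20); 30 | 5.1 (3.4 to 9.2) | 0.58 (−33 to 37) | 43% | 37% |
| c: 0 (20); 0 (25); 30 | 7.3 (3.9 to 35) | 0.20 (−36 to 32) | 48% | 43% |
| d: 0 (20); 0 (25); 3 | 0.75 (0.23 to 3.8) | −0.01 (−9.1 to 8.5) | 50% | 43% |
| e: 0 (15); 0 (20); 30 | 7.5 (4.6 to 22) | 0.42 (−40 to 38) | 46% | 41% |

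About 5% to 7% of denominators lie within one point of zero. In every scenario the mean of per-person ratios centres near zero, whatever the target.

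**3. The gate.** The chance that a paired comparison of costs at two-sided 5% is significant is Φ(d√120 − 1.96) + Φ(−d√120 − 1.96), where d is the standardised cost difference. This is a pairwise approximation to the three-method test. It gives 5%, 20%, 59% and 91% for d = 0, 0.1, 0.2 and 0.3. With small cost differences the formal comparison would often not be run, however different the accuracy.

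**The case against.** The best reply is that the protocol already has a sound route. The Measures section considers cost and accuracy together, checks dominance, and estimates the ratio if no method is dominated, all of which can be done with method-level means and without a significance gate. The mixed models under Energy Intake Estimation Accuracy report accuracy whatever the costs show. The two cost sections can also be read as successive steps, one on when to estimate and one on when to test. The gate would probably open anyway, since the mFR24 needs training, a researcher interview and coding, while the other two tools are self-administered.

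Most of this stands, and it limits the point. A reader might infer that cost-effectiveness cannot be obtained at all, or that a non-significant cost test would hide a clear winner. The documents support neither: only the tested comparison is lost or skipped.

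It is also fair to say that per-person averaging is inferred, because the protocol does not say how a per-person value would arise, and that instability is not peculiar to it. In scenario a the ratio of means ranges more widely than the mean of ratios. The difference is that the ratio of means is centred on roughly the right quantity and the other is not.

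The reply does not rescue the test. The Abstract and the Cost-effectiveness section both name ANOVA for cost-effectiveness, and if the gate opens the test still lacks a valid outcome variable. How participants with a missing day are handled is not fixed in the Cost-effectiveness section; it may be settled in an analysis plan and is no part of this point.

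**Conclusion.** The point holds in a limited form. The ANOVA of cost-effectiveness does not match the quantity the protocol defines, and the cost-significance gate does not match the trigger in the Measures section. The first conclusion follows from the definition alone and needs no assumed figure. On assumed inputs, averaging per-person ratios gives the wrong sign in 43% to 50% of runs; these figures are illustrative only.

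The gate is the lesser part. Design, sample size, data collection, and the cost and accuracy results for each method are unaffected. This should be fixed because cost-effectiveness is a headline aim, but it does not undermine the trial.

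**What to change.** Delete the ANOVA of cost-effectiveness and the condition on significant cost differences, and bring the Abstract and the Cost-effectiveness section into line with the Cost and Cost-effectiveness of Measures section. The ANOVA of time and financial costs can stay.

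For each pair of methods, estimate the mean paired difference in cost and in absolute percentage error in energy. Apply the dominance rule, then report incremental ratios between the methods that remain. Give uncertainty by bootstrapping participants, keeping each person's days together, and show it on the cost-error plane or as net benefit over a range of values per one-point reduction. A bare interval for the ratio is not enough, because the ratio of means is itself unstable when accuracy is close.

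The cost is a few sentences of protocol or analysis-plan wording and a participant-level bootstrap. No new data are needed.

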## Results

Participant recruitment commenced in March 2021 and will end in December 2021. Ethics approval for this study was granted by the Institutional Review Board in April 2019. Participant recruitment commenced in March 2021. As of August 2021, 68 participants had enrolled in the study. Data collection will conclude at the end of December 2021. Data analysis will commence in 2022, and results are expected to be published in late 2022.

